### Power calculation

One hundred-thirteen patients are currently followed by the Division of Pulmonary Disease in the University Hospital Geneva because of treatment with NIV and/or LTOT. We know that between one third and one half of these patients are hospitalized at least once during the year. Furthermore approximately 200 COPD patients per year are admitted to the Emergency Division of our hospital. Even if only a third of these patients are included in the study, this would give us sufficient statistical power to validly analyze our primary outcomes. Regarding the primary outcome, we calculated that a sample size of 80 patients per group would be adequate with an 80% power to detect a difference in hospital admissions of 20% between both groups at an α significance level (2-sided test) of 0.05.

With regard to missing data, we will use the conservative approach of carrying the last observation forward for all missing data in the intention-to-treat analyses. Poisson or binomial negative regression models will be used to compare count data between the groups while adjusting for potential confounder. The trend in the evolution of the different scores will be assessed using mixed linear regression models.

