## Background

Chronic obstructive pulmonary disease (COPD) is the fourth leading cause of mortality and the 12th leading disability worldwide
[1,2]. It is a progressive lung disorder with mortality rates between 36–50%, within 2 years after admission for an acute exacerbation
[3]. One out of eight (130,000) hospital admissions per year in the UK are related to COPD with approximately 30% of patients admitted with COPD for the first time being re-admitted within 3 months
[4].

While treatment with inhaled bronchodilators and steroids may partially relieve symptoms and Noninvasive Positive Pressure Ventilation (NIV) and long term oxygen therapy (LTOT) may prolong life, for many patients the course of the disease is one of inexorable decline with a prolonged period of disabling dyspnea and increasingly frequent hospital admissions reflecting deteriorating lung function and usually presaging a premature death
[5]. It has long been recognized that, in this group of patients, both quality of life and survival are poor. For instance, in the Nocturnal Oxygen Therapy trial of LTOT, disturbances in emotional and social functioning were common and there was a marked impairment in activities of daily living
[6].

Despite these issues, the needs of these patients are typically poorly addressed, and many patients have limited access to specialists in palliative care services
[7-10]. Furthermore many of these patients are housebound and they and their caregivers have poor access to health services. No randomised early palliative care intervention studies are available for this particular population, although it has been shown that it is feasible to provide palliative care interventions in this population
[11-15] A study conducted in the UK found that patients with COPD are much less likely to die at home and to receive palliative care services than patients with lung cancer
[7]. Additional studies have also documented the poor quality of palliative care and significant burden of symptoms among patients with COPD
[7,8,16-19]. In a retrospective cohort study conducted in Canada, of 1098 patients who died in 2004, very few patients who died with COPD used the palliative care services that were available in acute care hospitals (5.1%) or home care settings (2.8%) compared to those with lung cancer (acute care 47.6%; home care 37.4%)
[20].

Although anxiety and depression are common in COPD, they are not well recognized or treated

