### Outcomes measures

Regarding the primary outcome, Hospital, ICU and emergency admissions will be collected in both groups form the medical records once a month. Length of stay in the different divisions, type of divisions (i.e.: internal medicine, rehabilitation) and reasons for admissions will be collected.

Regarding the secondary outcomes of the study:

– Mood and anxiety of patients will be measured with the self-assessment instrument: the Hospital Anxiety and Depression Scale (HADS)
[50,51]

– Quality of life will be measured with the SF-36 short form: a self-assessment scale validated in this population, and the COPD Assessment Test (CAT): a short, simple instrument for quantifying the symptom burden of COPD in routine practice

– Use of antibiotics during the last three months will be recorded

– Completion of advance directives, documented preferences for resuscitation, or nomination of surrogate decision maker will also be recorded

The secondary outcomes will be collected at baseline and at weeks 12, 24, 36 and 48.

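### Last observation carried forward is prescribed for all missing data and called conservative, but in a progressive disease it can favour either arm and it distorts the score trends the planned mixed models are meant to estimate

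*Protocol article*

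**What the plan says.** The missing-data rule is one sentence in the Power calculation section: "we will use the conservative approach of carrying the last observation forward for all missing data in the intention-to-treat analyses". It exempts no outcome and gives no rule for patients who die.

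The next two sentences name the models. For counts: "Poisson or binomial negative regression models will be used to compare count data between the groups while adjusting for potential confounder". For scores: "The trend in the evolution of the different scores will be assessed using mixed linear regression models".

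Under Outcomes measures, the scores (HADS, SF-36, CAT) belong to the secondary outcomes: "The secondary outcomes will be collected at baseline and at weeks 12, 24, 36 and 48". The primary outcome has another source: "Hospital, ICU and emergency admissions will be collected in both groups form the medical records once a month". Data collection adds that place and date of death are taken from the medical records.

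The Background describes a course of steady deterioration for many patients and gives "mortality rates between 36–50%, within 2 years after admission for an acute exacerbation".

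**The concern.** Calling a missing-data method conservative promises that it will not manufacture a benefit. LOCF cannot promise that here. If scores worsen over time, a patient who leaves or dies is frozen at an earlier, better value. The more patients an arm loses, and the earlier, the better that arm looks.

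Unequal loss is plausible. The Discussion concedes that double-blinding is difficult. Under Intervention, only one arm has at least monthly nurse contact and telephone follow-up when a consultation is refused.

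The rule also works against the chosen model. A mixed linear model can use incomplete series as they are, under a missing-at-random assumption. Filling the gaps first with flat values bends the slope towards zero and counts copies as measurements.

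At stake are the mood and quality-of-life comparisons. Because the rule is stated positively for every outcome, an SAP that followed the protocol would inherit it.

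**Working it through.** The article gives no dropout rate and no figure for the effect of missing data, so there is no figure of its own to reproduce on this point. The sizes below are illustrations under stated assumptions.

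**1. Scores, closed form.**

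Inputs: four follow-up visits (Outcomes measures). Assumed: linear worsening of 1 point per visit (4 points by week 48), a constant chance of loss per visit, and no true difference between arms.

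If a proportion *d* is lost by week 48, retention per visit is r = (1 − d)^(1/4), and the mean LOCF change is r + r² + r³ + r⁴.

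- d = 25%: 0.931 + 0.866 + 0.806 + 0.750 = 3.35, against a true 4.
- d = 20%: 0.946 + 0.894 + 0.846 + 0.800 = 3.49.
- d = 35%: 0.898 + 0.806 + 0.724 + 0.650 = 3.08.
- 20% against 35%: 3.49 − 3.08 = 0.41 points in favour of the arm with more loss, where the truth is zero.
- Equal loss in both arms: difference zero.

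**2. Scores, error rate.**

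Simulation of 4,000 trials with 80 per arm (the figure in Power calculation). Assumed: total SD 1, decline of 1 SD over 48 weeks, no true effect, and a t-test on LOCF change from baseline.

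| Loss in the two arms | Bias between arms (SD) | Type I error |
|---|---|---|
| 25% / 25% | 0 | 4.9% |
| 30% / 20% | 0.07 | 7.4% |
| 40% / 20% | 0.14 | 16.2% |

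The bias in the last row follows from the formula in step 1: (3.49 − 2.94)/4 = 0.14, with 2.94 the sum for 40% loss.

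**3. Scores, with a true effect.**

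Assume the intervention slows the decline by 0.5 SD. LOCF then estimates:

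- 0.42 with 25% loss in each arm (0.5 × 3.35/4);
- 0.37 with 30% loss in control and 20% in intervention;
- 0.47 with 20% loss in control and 30% in intervention.

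The estimate therefore depends on which arm loses patients.

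**4. How much loss death alone might cause.**

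With a constant hazard, 36% to 50% over two years is 1 − √0.64 = 20% to 1 − √0.50 = 29% over one year. The source figure is for patients after an exacerbation admission. The Inclusion and exclusion criteria also admit patients without one, so this is not an expected rate for the cohort.

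**5. Admission counts, hypothetical only.**

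This step supposes that LOCF were applied month by month and past death. Assumed: 1 admission per year in ordinary months and annual mortality of 20% to 29%.

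| Admissions in the month of death | LOCF mean ÷ mean observed count | LOCF mean ÷ observed rate per year alive |
|---|---|---|
| As in any other month | 1.11 to 1.16 | 0.997/0.996 and 1.002/1.004, both 1.00 |
| 0.5 | 1.57 to 1.86 | 1.555/1.094 = 1.42 to 1.827/1.144 = 1.60 |

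So against the rate per year alive, any distortion comes entirely from an assumed excess of admissions before death. The article gives no figure for that excess.

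**The case against.** Several points on the other side stand.

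- **Admissions.** A reader might infer that the plan fabricates admissions for dead patients and so spoils the primary endpoint. The document does not support that. Counts come from medical records in both arms, at what Setting describes as the area's only public hospital. They do not depend on questionnaires being returned. Date of death is recorded, months after death are not strictly missing, and nothing says that a monthly count would be imputed. A carried value could also be zero.
- **Mixed models.** A reader might infer that LOCF and the mixed models contradict each other. They do not, since a mixed model can be fitted to filled-in data. It is a methodological inconsistency: the filling is unnecessary and harms the quantity being estimated.
- **Mortality.** The 36–50% cannot be carried over to the whole eligible cohort.
- **Score course.** Steady worsening of HADS, SF-36 and CAT over 48 weeks is an assumption. The Background speaks of the disease course in many patients, not of these scales.
- **Balanced loss.** With equal loss and no true effect, LOCF gives no between-arm bias and holds the error rate at the final visit. With a true slowing, it shrank the effect in all three scenarios of step 3. That is the sense in which it can be called conservative. The overstated precision concerns mixed models fitted to filled-in series; its size was not calculated.

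What remains is that nothing in the plan ensures balanced loss, and the direction of the bias depends on that.

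**Conclusion.** The point holds for the scores. LOCF is a stated rule, it is not conservative, and it feeds flat, invented values into models chosen to estimate trends, including values after death. Under an assumed linear worsening of 4 points, 25% loss shrinks the change to 3.35, and 20% against 35% loss creates a false difference of about 0.4. In the simulation, type I error was 7.4% at 30%/20% loss and 16.2% at 40%/20%. These sizes rest on the assumed decline, hazard and loss rates. The conclusion that the bias can go either way needs only a trend in the scores and unequal loss.

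For the primary outcome there is a wording gap and no demonstrated distortion. The phrase covering all missing data does not exclude the counts, and it should.

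**What to change.** 1. Delete the LOCF sentence, including the word conservative.
2. Analyse HADS, SF-36 and CAT with the planned mixed model on all observed visits, and impute no values after death. A missing-at-random model still extrapolates implicitly beyond death, so state what the estimate means in the presence of death.
3. Add one missing-not-at-random sensitivity analysis, for example delta-adjusted multiple imputation for missingness not due to death.
4. State that admissions are analysed as observed counts, with an offset for time alive and under observation and no imputed months. An offset alone treats death as uninformative, so report deaths by arm alongside and add a sensitivity analysis with death as a terminal event.

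The change should be made before outcomes are seen by arm. It costs some wording and a little more analysis. It needs no new data, since date of death is already collected, and the stated sample size is unaffected.

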## Abstract

**Background:**

COPD is a progressive lung disorder with rates of mortality between 36–50%, within 2 years after admission for an acute exacerbation. While treatment with inhaled bronchodilators and steroids may partially relieve symptoms and oxygen therapy may prolong life, for many patients the course of the disease is one of inexorable decline. Very few palliative care intervention studies are available for this population. This trial seeks to determine the effectiveness of the introduction of specialized palliative care on hospital, intensive care unit and emergency admissions of patients with severe and very severe COPD.

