### Intervention

The theoretical basis of the intervention was established by reviewing the published literature on the impact of the early introduction of palliative care in patients with severe diseases
[7,8,12,14,16-18,22,24,32-34,39-49]. Information gathered in this phase has been used to develop the optimal intervention by a multidisciplinary group and a study design adapted to our regional health system. Researchers involved in the recruitment of the patients are blinded to the details of the intervention. Our team also established contacts with experts who had already developed specialized palliative care interventions in this type of population.

Patients assigned to the early palliative care group will meet a nurse attached to the community ambulatory palliative care unit of the HUG (USPC) within three weeks of inclusion and at least monthly thereafter during one year after inclusion. This nurse has a long experience in palliative care. The first consultation will take place at the patient’s home, unless the patient prefers to have the consultation at the pulmonary division. It will take approximately 1 h ½ to assess and discuss the different items. The subsequent monthly consultations will last approximately 30 minutes according to the needs of the patients. A consultation with a specialized palliative care physician or another specialist (psychiatrist, pulmonologist….) will be organized if intensity of pain, dyspnea, mood, anxiety and appetite disturbances are >4/10 on visual analogic scales (VAS) and both the patient and his/her physician agree. The individualised palliative care assessment and treatment plan will be forwarded in writing to the physician in charge of the patient within 24 hours of the consultation. These consultations will be at charge of the insurance of the patient. Details of the palliative consultation are described in Table 
1. We decided to establish a set of core interventions, but not to schedule these different items to respect the rhythm and needs of the patients. At the end of each consultation, the items discussed during the consultations will be collected. Participants who refuse to attend one or more palliative care interventions will be contacted by phone by the palliative care nurse to understand their reasons. If the patient, agrees a new appointment will be fixed.

**Table 1 T1:** Description of the palliative care intervention

1.	**Symptom management**

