### Data collection

Baseline data will be collected in each patient’s home by the study nurse. The timing of interventions and data collection has been designed to not be too burdensome in this population with a severe disease
[15].

The baseline characteristics of the participants that will be measured are:

– Socio-demographic items: age, sex, marital status, education, children, living condition

– Smoking habits, weight, height, co-morbidities measured by the CIRS
[52], activities of daily living
[53], artificial nutrition (enteral, parenteral), prescribed treatment

– health professionals who participated to their care over the past three months (ie: nurses , dietician, occupational therapist)

– Additional equipment such as electric bed, wheelchair

– Characteristics and management of COPD: pulmonary function tests, oxygen saturation, use of oxygenotherapy, use of NIV, pharmacological treatment, numbers of acute exacerbations, admissions to emergency room, intensive care unit and hospital over the past three months Location and date of death will be collected from the medical records

Most of these data will be collected during the collection of primary and secondary outcomes (at weeks 12, 24, 36 and 48).

Data will be collected in computer files and will be rendered anonymous, without any reference to initials. Only the principle investigator will have the key to the correspondence between patient reference number and identity. The CRF (case report form) will be collected using SecuTrial software with the support of the Clinical Research Center, Geneva University Hospitals ([name]). A clinical research fellow, allocated for this project will adapt the data base and enter the data in the SecuTrial software.

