### Statistics

To compare baseline characteristics and study outcomes of the patients between groups, Fishers’ exact tests, chi-square tests and the independent-samples t-test or the non-parametric equivalent Mann–Whitney u test will be used.

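### The stated analysis of admissions gives time alive and mortality no role, so a difference in deaths between arms would bias it, in a direction that depends on how carry-forward is read

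*Protocol article*

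**What the plan says.** All references are to the protocol article.

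- **Outcomes measures** (primary outcome): "Hospital, ICU and emergency admissions will be collected in both groups form the medical records once a month". Length of stay is recorded too.
- **Statistics**: baseline characteristics and study outcomes are to be compared by Fisher's exact and chi-square tests, and the "independent-samples t-test or the non-parametric equivalent Mann–Whitney u test will be used".
- **Power calculation**: Poisson or negative binomial models "will be used to compare count data between the groups while adjusting for potential confounder". No offset, person-time or follow-up time is mentioned, and none is ruled out.
- **Power calculation**, missing data: the rule, which the article calls conservative, is "carrying the last observation forward for all missing data in the intention-to-treat analyses". Death is not set apart.
- **Background**: the disease is described as having "mortality rates between 36–50%, within 2 years after admission for an acute exacerbation".
- **Data collection**: "Location and date of death will be collected from the medical records". Survival appears neither among the objectives nor under Outcomes measures, and date of death is given no part in the analysis.
- **Intervention**: nurse visits run "at least monthly thereafter during one year after inclusion". Secondary outcomes are assessed up to week 48.

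**The concern.** A patient who dies in month 2 can contribute only two months of admissions. On a raw total, that patient may look better than one who lives the full year and is admitted twice. This does no harm to the comparison if deaths are equally frequent and equally timed in the two arms. It biases the comparison if they are not.

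A difference in survival, in either direction, is plausible here. According to Table 1, the intervention covers preferences for end-of-life care, with hospitalisation as the example, and advance directives. If the trial then finds fewer admissions, the reader will want to know whether patients were admitted less often while alive or were alive for less time. None of the analyses named in the article separates the two.

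The carry-forward rule adds a second problem. It covers all missing data, so read literally it also fills the months after death, and the article does not say which value is carried. The direction of any bias depends on that choice.

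**Working it through.** **1. One-year mortality implied by the protocol's figures.** Assuming a constant hazard, one-year mortality = 1 − √(1 − two-year mortality).
- 36%: 1 − √0.64 = 0.20
- 50%: 1 − √0.50 = 0.29

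**2. Mean time alive within one year.** T(p) = p / (−ln(1 − p)), where p is one-year mortality.

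| p | T (years) |
|---|---|
| 15% | 0.923 |
| 20% | 0.896 |
| 29% | 0.847 |
| 30% | 0.841 |
| 40% | 0.783 |

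**3. Apparent ratio of cumulative counts with no true effect.** If the admission rate while alive is the same in both arms, the ratio is T(arm with more deaths) / T(other arm). The arm-specific mortalities are assumptions; the article gives none.
- 20% vs 25%: 0.97
- 20% vs 29%: 0.847/0.896 = 0.94
- 15% vs 30%: 0.841/0.923 = 0.91
- 20% vs 40%: 0.783/0.896 = 0.87
- A ratio of 0.80 from deaths alone needs about 20% vs 51%.

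**4. Frailty shared by death and admission.** Let each patient's hazard of death h and admission rate both be multiplied by the same gamma frailty (mean 1, variance 1; assumed). The expected count is then proportional to 1/(1 + h), with h = −ln(1 − p).
- p = 20%, 30%, 40%: h = 0.223, 0.357, 0.511, so 1/(1 + h) = 0.818, 0.737, 0.662.
- Apparent ratios: 0.737/0.818 = 0.90 and 0.662/0.818 = 0.81.
- Here p is mortality at average frailty. Mortality in the whole arm is 1 − 1/(1 + h), or about 18%, 26% and 34%.

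**5. Simulation with and without an offset.** 90 per arm (the abstract's figure), 2 admissions per year (assumed), frailty variance 1, 1,000 runs, negative binomial regression with dispersion fixed at 1, true rate ratio 1. Shared-frailty results are in brackets.

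| Mortality | Ratio, no offset | Ratio, log(time alive) offset | False positives, no offset | False positives, offset |
|---|---|---|---|---|
| 20% vs 20% | 1.00 (1.01) | 1.00 (1.01) | 6% (6%) | 5% (6%) |
| 20% vs 30% | 0.94 (0.90) | 1.00 (0.96) | 7% (9%) | 5% (5%) |
| 20% vs 40% | 0.87 (0.81) | 1.00 (0.93) | 13% (21%) | 5% (7%) |

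The Mann–Whitney test on totals gave 5% (9%) false positives at 20% vs 30% and 10% (17%) at 20% vs 40%. The offset removes the bias when death and admission are independent, and only part of it when they share a cause.

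**6. Carry-forward after death.** If the cumulative count is carried, steps 3 to 5 apply. Suppose instead that the last monthly count is repeated, and that half of those who die had one admission in their final month (assumed). The months after death are then filled at 0.5 per month, or 6 per year, against 2 per year otherwise. Leaving out the extra admissions of the final month itself:
- 20% mortality: 2 × 0.896 + 6 × 0.104 = 2.42
- 40% mortality: 2 × 0.783 + 6 × 0.217 = 2.87
- Ratio: 2.87/2.42 = 1.19

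The arm with more deaths now appears to have more admissions.

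**The case against.** **The missing offset is silence, not a decision.** Poisson and negative binomial models routinely carry a log-time offset, nothing in the article excludes one, and a condensed article may leave such detail to the full protocol or analysis plan. This stands for the regression. A reader might infer that the plan compares raw totals and rules out time at risk; the text does not say so. The objection does not reach the t and Mann–Whitney tests or the carry-forward rule, which are written down. The two tests have no place for an offset, and the rule makes no exception for death.

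**A death need not look like a success.** The Background reports that patients with COPD often die in intensive care, so death may come with the very admissions being counted. This stands in part. Under the step 6 assumption, each death adds 0.5 − 2/12 = 0.333 admissions in the final month. At 20% vs 29% mortality the cumulative counts become 1.792 + 0.067 = 1.859 and 1.694 + 0.097 = 1.791, a ratio of 0.96 rather than 0.94.

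**The mortality contrasts are generous.** This stands. The cited range applies after an exacerbation admission, whereas patients can also enter on lung function, home oxygen or ventilation. Placing its two ends in the two arms implies a death hazard ratio of 0.342/0.223 = 1.5; 15% vs 30% implies 0.357/0.163 = 2.2. The article supports neither.

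**The trial could still separate the two explanations.** Also correct. Dates of death, monthly admissions and lengths of stay are collected, so rates per time alive and mortality by arm can be produced. The gap is in the stated analysis, not in the data.

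**Conclusion.** The point holds in limited form and should be fixed. Deaths are expected to be common, the tests named for study outcomes cannot take account of time alive, the count model states no exposure term, and carry-forward does not except death. If mortality differs by arm, the comparison of admissions is biased.

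With cumulative counts the bias favours the arm with more deaths: about 0.94 at 20% vs 29% and 0.91 at 15% vs 30%, with no true effect. These figures assume a constant death hazard, one year of follow-up, an admission rate unrelated to dying, and arm-specific mortalities that the article does not give. Shared frailty makes the bias larger; admissions just before death make it smaller. The effect on the false-positive rate is small until mortality differs widely.

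Two stronger readings are not supported:
- **That the bias always flatters the arm with more deaths.** If the last monthly count is repeated after death, the direction may reverse, so neither the direction nor the article's description of the rule as conservative is established.
- **That the bias is a stated fraction of the 20% effect sought.** This would need 20% to be a relative reduction in counts. The 80 per group in Power calculation fits 20 percentage points instead: 40% vs 20% needs 82 per group, whereas a relative reduction from a control proportion of one third to one half needs 388 to 741.

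**What to change.** Before the analysis:

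1. Name the count regression as the decisive primary analysis, with log(days alive and under follow-up within the follow-up year) as offset. Do not let t or Mann–Whitney tests on raw totals decide.
2. State that time after death is not missing data and is excluded from carry-forward. An offset without this step would leave the written rule in force.
3. Report all-cause mortality by arm beside the primary result.
4. Because an offset does not fully remove the bias when death and admission share causes, add one supportive analysis that treats death as a terminal event. Days alive and out of hospital is one suitable choice; a joint model of admissions and death is another.

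The cost is analysis wording and a few tables. Dates of death, admissions and lengths of stay are already collected, so no new data are needed. If the full protocol or analysis plan already specifies the offset, items 2 to 4 should still be checked against it.
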